### Data management

The first researcher ([name]) will be responsible for monitoring the collection and quality of data as well as the participant recruitment and retention. All data collected will be kept strictly confidential, accessed only by members of the trial team, and stored on a secure computer with passwords. Each participant will be allocated an individual trial identification number.

### Statistical analysis

All data will be analyzed by SPSS version 26 software (IBM Corporation, Armonk, NY, USA). Descriptive statistics, such as frequencies and percentages of categorical variables and mean, standard deviation, median, and range values of linear variables, will be used. To gain insight into the relative factors of PA, descriptive statistics will be calculated to describe participants’ demographic characteristics, gestational weight gain, PA level, and PA self-efficacy during pregnancy. Primary analyses, including chi-squared and independent *t* tests, will be used to examine group differences in the primary and secondary outcomes. Repeated analysis of variance will be used to assess within-patient correlations. By using a series of mixed-effects regression models with a likelihood-based approach, we will regress the score of PPAQ at follow-up to determine the effect on the baseline, group, time, group × time, and confounders identified in the preliminary step. Effect sizes will be reported with 95% confidence intervals, and results will be considered significant if *P* < 0.05. The analysis of the primary and secondary outcomes will be based on an intention-to-treat basis [59], which will include study withdrawals and losses to follow-up.

## Discussion

PA throughout pregnancy has been proven safe and beneficial for both women and fetuses. However, women at higher risk for GDM spent most of their time performing sedentary behaviors rather than PAs [21]. Although researchers have identified self-efficacy as a mediator to overcome PA barriers [31, 32], exercise intervention during pregnancy based on self-efficacy theory has not been discussed so far. Furthermore, there is conflicting evidence regarding the positive effect of exercise in women at higher risk for GDM on the incidence of GDM and other maternal or neonatal outcomes. With the development of China's second-child and third-child policies, there will be more and more pregnant women with complex high-risk factors for GDM. Our proposed randomized controlled trial will provide important additional information on the effect of self-efficacy theory-oriented exercise programs on pregnant women with multiple high-risk factors for GDM.

This study has several strengths. First, it targets pregnant women at high risk for GDM. Other strengths of our study include the development of intervention sessions based on self-efficacy theory; the thorough testing of pregnant women as well as their newborns; and the investigation of possible effects of exercise training on PA level, the incidence of GDM, and gestational weight gain. In addition, the composition of the exercise program includes both aerobic and resistance training. Because of the convenience and ease of access, WeChat was selected as the delivery channel for the exercise video and exercise diary. Moreover, we conducted a process evaluation following the guidance of Medical Research Council guidelines.

The limitation of this study is that the PA level will be evaluated by a questionnaire without objective equipment. Guidelines about PA for pregnant women recommend subjective assessments as the first choice to evaluate exercise status as they are handy and personalized [18]. We will ask our study participants to keep an exercise diary, including comments on walk steps and their feelings while exercising. The data above will be involved in the process evaluation. Primary risks at the participant level will include failure to persist with PA with standard posture for the movements or forgetting to exercise. To mitigate against these risks, participants will receive training regarding how to follow the exercise video at home and how to complete their exercise diary on the WeChat platform. We will also offer some tips to remind them to exercise and record their experience, such as setting a clock alarm, putting notes on the refrigerator or television to reduce sedentary time, and being active. Moreover, researchers will send reminder messages every morning or evening to the WeChat group to remind participants to exercise.

According to the World Health Organization [60], some PA are better than none for pregnant women. The results from this study will provide grounds for giving advice as well as organizing exercise training groups for women with high-risk factors for GDM. If the women randomized to the exercise program achieve positive effects in any primary or secondary outcome compared to controls, the addition of this program to the regular pregnancy care for high-risk individuals should be considered.

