**Methods/design:**

A single-center, parallel, randomized controlled trial will be conducted in a maternal–child health care center. A total of 244 pregnant women at high risk for GDM will be randomized into a study group receiving a self-efficacy-enhancing physical activity intervention or a control group receiving the usual care. The intervention will consist of four group sessions and everyday reminders by WeChat (Tencent, Shenzhen, China). The program will begin at approximately 13–14^+6^ gestational weeks and end at 36^+6^ gestational weeks. The primary outcomes will include the incidence of GDM, blood sugar values, and physical activity. The secondary outcomes will include physical activity self-efficacy, gestational weight gain, maternal outcomes, and neonatal outcomes.

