### Sample size

The sample size of this study was calculated based on recent research available on the impact of PA on the incidence of GDM in Chinese overweight and obese pregnant women. Using information from that study [38] documenting incidence rates of GDM of 22% in the intervention group after PA intervention and 40.6% in the control group, we found that a sample size of a ≥ 98 women in each arm of this study will be required to detect a difference in the incidence of GDM between groups (80% power and *α* = 0.05). The treatment and control ratio is 1:1. Allowing for 20% attrition during pregnancy, ≥ 122 women in each arm will need to be recruited.

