### Outcome measures and data collection

The list of data-collection instruments and times of data collection are presented in Table 4. The primary outcomes of this study are blood sugar values during the 75-g oral glucose tolerance test, the incidence of GDM at 24–28 weeks’ gestation, and PA levels at 24–28 and 35–37 weeks’ gestation. The secondary outcomes include PA self-efficacy, gestational weight gain, maternal outcomes, and childbirth outcomes.

**Table 4 Tab4:** Data collection instruments and time of data collection

	Booking		24–28 weeks’ gestation		35-37 weeks’ gestation		Within 3 days after delivery	
	IG	CG	IG	CG	IG	CG	IG	CG

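### Three alternative primary outcomes share one P < 0.05 threshold with no stated hierarchy, and the Discussion lets a positive effect on any outcome support adding the programme to care

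*Protocol article*

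**What the plan says.** The Abstract states: "The primary outcomes will include the incidence of GDM, blood sugar values, and physical activity". The section Outcome measures and data collection repeats this: "The primary outcomes of this study are blood sugar values during the 75-g oral glucose tolerance test, the incidence of GDM", followed by PA levels at 24–28 and 35–37 weeks. It then lists PA self-efficacy, gestational weight gain, maternal outcomes and childbirth outcomes as secondary.

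In Statistical analysis, chi-squared and independent t tests "will be used to examine group differences in the primary and secondary outcomes", and "results will be considered significant if *P* < 0.05". No outcome is placed ahead of another. A mixed-effects model is also planned for the PA questionnaire score.

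In Sample size, at least 98 women per arm "will be required to detect a difference in the incidence of GDM between groups". No other outcome enters the calculation.

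The Discussion closes with a condition: "If the women randomized to the exercise program achieve positive effects in any primary or secondary outcome compared to controls". Its consequence is that adding the programme to regular care for high-risk women should be considered.

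**The concern.** A 5% significance level protects one test. Here several outcomes are declared primary, success on any one of them appears to be enough, and the Discussion extends the same latitude to every secondary outcome. The more chances there are to succeed, the more often an ineffective programme yields something to point to.

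The kind of outcome that could succeed also matters. PA is self-reported by questionnaire. The women know their allocation (Randomization and blinding), and only the intervention arm is reminded daily to exercise and asked to keep an exercise diary (Intervention). A difference in reporting could therefore produce a positive PA result with no change in GDM, the question the trial was sized to answer. Under the Discussion sentence, that result alone would be enough.

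**Working it through.** **The plan's own figure.** Inputs from Sample size: 22% against 40.6% GDM, α = 0.05, 80% power, 1:1 allocation. Sidedness is not stated, but the two-sided formula reproduces the figure. The mean proportion is 0.313 and the difference 0.186.

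n per arm = 2 × 0.313 × 0.687 × (1.960 + 0.842)² / 0.186² = 97.6, so 98, as stated. Power at 98 per arm (pooled variance under the null, unpooled under the alternative) is 80.7%. The stated size is right for one test of GDM at 0.05.

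**Counting tests (my count).**
- Primary: GDM 1; OGTT 3 (fasting, 1 h, 2 h); PA 2 (two follow-ups). Total 6.
- Secondary: self-efficacy 2 (two follow-ups); weight gain 1; maternal 5; neonatal 11. Total 19.
- All: 25. PA intensity categories and the mixed models are not counted.

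**Error rate.** The Discussion speaks of positive effects, so I count only results that favour the programme, giving 0.025 per test. For k independent tests the chance of at least one is 1 − 0.975^k:
- k = 6: 1 − 0.975⁶ = 14.1%
- k = 25: 1 − 0.975²⁵ = 46.9%

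The documents give no correlations. Assuming equal pairwise correlation ρ between normal test statistics (400,000 simulated draws):

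| Tests | ρ = 0 | ρ = 0.3 | ρ = 0.5 | ρ = 0.7 |
|---|---|---|---|---|
| 3 (one per primary family) | 7.3% | 6.9% | 6.3% | 5.4% |
| 6 primary | 14.1% | 12.2% | 10.3% | 8.2% |
| 25 primary and secondary | 46.9% | 31.8% | 23.4% | 15.8% |

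The reference rate for one test in the favourable direction is 2.5%. A second simulation of the six primary tests at 98 per arm derived GDM from the three glucose values (40.6% in both arms) and used assumed correlations of 0.3–0.7. It gave 11–13%, inside the six-test range.

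**PA alone.** As an illustration, suppose reporting by itself shifts the PA score by 0.2 to 0.4 SD (assumed). With 98 per arm, the standardised shift is 0.2 × √(98/2) = 1.4 to 0.4 × √(98/2) = 2.8. The chance of a favourable P < 0.05 is then Φ(1.4 − 1.96) ≈ 29% to Φ(2.8 − 1.96) ≈ 80%.

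**Keeping three primaries with a Bonferroni split.** α = 0.05/3 = 0.0167. GDM power at 98 per arm falls from 80.7% to 66%. Restoring 80% needs 129 per arm, or 129/0.8 ≈ 162 with the plan's 20% attrition.

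**The case against.** Four stronger readings are tempting, and the text does not bear them out.

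- A reader might infer that any positive result triggers adoption. The sentence is closing Discussion prose, says only that adoption should be considered, and does not define a positive effect as P < 0.05. It is a loosely worded route to a recommendation, not a formal rule in the analysis section.
- A reader might infer that every test is declared unadjusted. The article gives a threshold and no hierarchy. It does not say that P values are unadjusted, and a multiplicity procedure may sit in an analysis plan not shown here. Hence the error rates above are conditional on each outcome being tested at 0.05. Even so, a procedure covering the primary outcomes would not repair a sentence that admits any secondary outcome.
- A reader might call these co-primary outcomes. In the strict sense that means all must succeed, which does not inflate the error rate. These are alternative primaries.
- A reader might lead with two-sided rates: 26% over six independent tests, 72% over 25. Those also count results favouring control, which the Discussion sentence does not.

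The counts can also be contested. The 25 are tests, not distinct outcomes, and the mixed model could reduce PA to one group effect. With one test per primary family the rate is 5.4–7.3%: smaller, but still at least twice 2.5%. Equal correlation across all 25 is a simplification, and some secondary outcomes, such as mode of delivery, have no single favourable tail.

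Self-report bias is strictly a separate matter from multiplicity, and the Discussion already concedes the lack of objective measurement. It belongs here only because the Discussion sentence lets that outcome carry the recommendation. Finally, the objectives in the Background put GDM, glucose and PA level side by side, so ranking PA below GDM is a choice with a price.

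**Conclusion.** The point holds in this form. The article fixes three alternative primaries, one threshold, no stated order among outcomes, and a sentence that accepts success on any of them, while its sample size supports a claim on GDM only.

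If each outcome is tested at 0.05, the chance of a falsely favourable result is about 8–14% over six primary tests and 16–47% over about 25. That is roughly 3 to 6 times and 6 to 19 times the nominal 2.5%. The lower ends assume a correlation of 0.7 between all tests, which is generous for outcomes as unlike as fasting glucose and Apgar score. The exact size depends on the assumed counts and correlations, but the inflation remains throughout that range.

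**What to change.** 1. Name GDM incidence at 24–28 weeks as the single primary outcome, tested two-sided at 0.05. The 98 analysed and 122 recruited per arm stand, with power about 81% at 98.
2. Make OGTT values and PA key secondary outcomes under a prespecified Holm or fixed-order procedure. State whether that procedure opens only if GDM is significant; strict gating is defensible but debatable, because it bars a confirmatory PA claim when GDM misses.
3. Report the remaining outcomes as supportive, with 95% confidence intervals.
4. Reword the Discussion sentence so that recommending the programme rests on a reduction in GDM.
5. Date the change, make it before unblinded outcome data are seen, and notify investigators, ethics committees and the registry, as Study design commits. Trial status says recruitment began in February 2022, so this is a mid-trial change to declared primaries and must be documented as one.

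No extra participants are needed. The cost is fewer confirmatory claims on PA, glucose and the secondary outcomes, plus the documented amendment. If the sponsor prefers to keep all three families as primary, a Bonferroni split leaves GDM power at about 66% at 98 per arm. Holm, with one summary test per family, gives between that and 81%, depending on the other two results. Either way, the power statement would have to be restated.

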## Conclusion

This paper describes how we plan to implement a theory-based PA program during pregnancy to reduce the incidence of GDM and improve the PA level, PA self-efficacy, and gestational weight gain. We will also conduct a process evaluation. The effectiveness of the proposed program will be investigated in the future in a randomized controlled trial. The results will speak to whether a low-touch, mobile technology intervention can effectively reduce the incidence of GDM and improve PA, PA self-efficacy, and gestational weight gain in pregnant women suffering at high risk for GDM. The results could inform the development and implementation of broadly reaching interventions in the community, academic, and clinical settings and could thus play an important role in the effort to improve the health of pregnant women and newborns.

## Trial status

This study is approved by the Chinese Clinical Trial Registry (CHiCTR): (protocol ChiCTR2200056355). Recruitment commenced in February 2022. It is expected to be completed by October 2022. Data collection will be completed by February 2024.

## Data Availability

The datasets analyzed during the current study are available from the corresponding author on reasonable request.

## Abbreviations

BMI: Body mass index
GDM: Gestational diabetes mellitus
GWG: Gestational weight gain
LGA: Large-for-gestational-age
MET: Metabolic equivalent of task
PA: Physical activity
P-ESES: Pregnancy Exercise Self-efficacy Scale
PPAQ: Pregnancy Physical Activity Questionnaire
SGA: Small for gestational age
